## Abstract

**Background:**

Currently available disease-modifying treatments acting by modifying the immune response are ineffective in progressive multiple sclerosis (MS), which is caused by a widespread axonal degeneration. Mechanisms suspected to be involved in this widespread axonal degeneration are reduced axonal energy metabolism, axonal glutamate toxicity, and reduced cerebral blood flow. Fluoxetine might theoretically reduce axonal degeneration in MS because it stimulates energy metabolism through enhancing glycogenolysis, stimulates the production of brain-derived neurotrophic factor, and dilates cerebral arterioles. The current document presents the protocol of a clinical trial to test the hypothesis that fluoxetine slows down the progressive phase of MS.

**Methods/Design:**

The FLUOX-PMS trial is a multi-center, randomized, controlled and double-blind clinical study. A total of 120 patients with the diagnosis of either secondary or primary progressive MS will be treated either by fluoxetine (40 mg daily) or placebo for a total period of 108 weeks. The primary endpoint is the time to confirmed disease progression defined as either at least a 20% increase in the timed 25-Foot Walk or at least a 20% increase in the 9-Hole Peg Test. Secondary endpoints include the Hauser ambulation index, cognitive changes, fatigue, magnetic resonance imaging of the brain, and in a small subgroup optical coherence tomography.

**Discussion:**

The FLUOX-PMS trial will gives us information as to whether fluoxetine has neuroprotective effects in patients with progressive MS.

**Trial Registration:**

Eudra-CT: 2011-003775-11

## Background

Multiple sclerosis (MS) is a chronic inflammatory and degenerative disease and is considered the most important non-traumatic cause of neurological disability in young adults. Despite many decades of intensive research, the cause of MS has remained elusive, and many aspects of the pathogenesis are not understood. The disease appears to precipitate in genetically susceptible individuals, very likely as a result of an environmental trigger. An infectious component has long been suspected, but no specific transmissible agent has so far been linked convincingly to MS [1].

The disease course of MS is heterogeneous. A majority of patients initially has bouts of neurological deficit (relapses) followed by (partial) recovery (the so-called ‘relapsing remitting’ stage). This stage is often followed by a slowly progressive increase in disability (the stage of ‘secondary progression’). Other patients develop progressive increase in neurological disability from onset, without obvious relapses and remissions (‘primary progressive form’) [1].

Focal inflammatory demyelinating lesions that develop in eloquent areas within the CNS cause relapses. The progressive phase of MS, either secondary or primary, reflects a poorly understood insidious widespread axonal degeneration that is age-related and independent of relapses [2-4]. Currently available disease-modifying treatments, which act by modifying the inflammatory response, reduce the frequency of relapses, but are not effective in progressive MS [5-7].

Astrocytes in MS appear to be deficient in ß_2_ adrenergic receptors [8], which activate a Gs protein that associates with adenylate cyclase, leading to the conversion of ATP to cAMP, which in turn activates protein kinase A (PKA). Norepinephrine, via the stimulation of ß_2_ adrenergic receptors, tightly suppresses the expression of interferon γ-induced MHC class II molecules on cultured astrocytes [9]. We have proposed that downregulation of ß_2_ adrenergic receptors on astrocytes in MS may alter the phenotype of astrocytes into facultative immunocompetent antigen presenting cells that can initiate the inflammatory reactions leading to demyelination [10,11]. Fluoxetine activates PKA in astrocytes [12], and might thus compensate for the astrocytic ß_2_ adrenergic receptor deficiency. Based on this hypothesis we performed a pilot study in patients with relapsing remitting MS and found that a daily dose of 20 mg tended to reduce the formation of new inflammatory lesions on magnetic resonance imaging (MRI) of the brain [13].

Mechanisms proposed to be involved in the progressive axonal degeneration in MS are reduced axonal energy metabolism, axonal glutamate toxicity, and reduced cerebral blood flow [14-16]. This might also be mediated by astrocytic dysfunction, associated with reduced astrocytic ß_2_ adrenergic receptors [11]. Fluoxetine might reduce progressive axonal loss in MS, through activation of PKA, as it stimulates astrocytic glycogenolysis necessary for maintenance of sodium-dependent glutamate uptake by astrocytes, and the release of lactate, which serves as energy source for axons [17,18]. Fluoxetine also stimulates the release of the neuroprotective brain-derived neurotrophic factor (BDNF) from astrocytes [18], and may improve cerebral blood flow by dilating cerebral arterioles independent of the endothelium [19].

Two weeks of treatment with fluoxetine (first week 20 mg/day and second week 40 mg/day) significantly improved cerebral white matter N-acetylaspartate/creatine ratio in MS patients, suggesting an improvement in axonal mitochondrial energy metabolism, because N-acetylaspartate is produced by mitochondria [20].

Based on these preliminary findings we decided to perform a randomized placebo-controlled trial to assess whether fluoxetine has a neuroprotective effect in patients with progressive MS.

Secondary and primary progressive MS have a different form of symptom onset but the underlying pathophysiological mechanism leading to progressive axonal degeneration is likely the same. It is independent of relapses, and the progressive phases of each proceed at remarkably similar rates [1]. In addition the difference between the progressive types is not always clear cut and often arbitrary as subjects with primary progressive MS can also experience relapses.

## Methods/Design

### Trial design

FLUOX-PMS (FLUOXetine in Progressive Multiple Sclerosis) is a multi-center, randomized, controlled parallel group, and double-blind clinical trial conducted at different sites located in the Flemish region of Belgium, and in The Netherlands. Recruitment in Belgium and The Netherlands started in February 2012 and April 2013, respectively. In total, 120 patients with either secondary or progressive MS will be randomized to receive either two tablets of fluoxetine 20 mg or placebo of identical appearance, daily for 108 weeks. The study is approved by the local ethics committees (See Additional file 1) and at the national level by ‘Federaal Agentschap voor Geneesmiddelen en Gezondheidsproducten’ (Belgium) and the ‘Centrale Commissie Mensgebonden Onderzoek’ (Netherlands). The study is registered at the European Union Drug Regulating Authorities (Eudra-CT: 2011-003775**-**11). The study will be conducted in accordance to the Declaration of Helsinki in its currently applicable version, the guidelines of the International Conference on Harmonization of Good Clinical Practice (ICH-GCP), and the applicable Belgian and Dutch legislation. All participants are required to give written informed consent.

### Participants

Inclusion criteria for participation in the FLUOX-PMS trial comprise the diagnosis of either secondary or primary progressive MS according to the revised 2010 McDonald criteria [21], aged 25 to 65 years, a score between 3 and 6.5 included on the Expanded Disability Status Scale (EDSS) [22], and documented confirmed evidence of disease progression independent of clinical relapses over the 1 year prior to enrolment, defined as an increase of 0.5 point on the EDSS. For sexually active female patients with reproductive potential, use of reliable means of contraception is required. The main exclusion criteria include use of antidepressants. Concomitant medications that may lead to clinically significant interactions with fluoxetine (such as monoamine oxidase inhibitors that could lead to a serotonin syndrome) are not allowed. Other exclusion criteria are pregnancy or lactation, other neurologic, serious psychiatric (for example, major depression) or systemic disorders that may interfere with the assessments. Use of immunomodulatory or immunosuppressive drugs is not allowed, except for interferon beta or glatiramer acetate, as it has been shown that these drugs are ineffective in slowing down progression [5-7]. Patients using other immunosuppressive or immunomodulatory drugs can only be included if stopped at least for 2 months before randomization.

### Study mediation, randomization, and follow-up

Eligibility of patients is determined at the screening visit (week −4). At baseline visit, patients who qualify for participation in the study are randomized 1:1 using a block size of 10, to receive either fluoxetine or placebo. Study medication (verum and placebo) was purchased from Eurogenerics and stored at the department of Pharmacy of the UZ Brussel. After inclusion, patients are given a computer-generated randomization number, which is matched to a confidential treatment number by the study pharmacist of the UZ Brussel to assign patients either to fluoxetine or to placebo.

Trained study nurses visit patients at home to perform all assessments in their natural environment, avoiding the stress and efforts of going to the hospital, which may interfere with clinical assessments. They plan the brain MRI scans, provide the study medication, and will be contacted in case of adverse events, suspected relapse, or questions. Counting tablet returns at each visit will assess adherence. In case of a suspected relapse they will refer the patient to their treating neurologist. All patients are followed as usually by their treating neurologist. When there is a change in immunomodulatory treatment or antidepressants have to be started, the treating neurologist is kindly asked to notify the study team.

Regular study visits are carried out at weeks 0, 12, 24, 36, 48, 60, 72, 84, 96, and 108. An optional follow-up visit will be offered at week 120 to confirm sustained progression appearing at week 108. If necessary, additional unscheduled visits can be performed at any time. The study flow-chart is shown in Figure 1.

**Figure 1 F1:**
[figure not shown]
Trial flow chart (see also list of abbreviations).

### Primary outcome parameter

The primary endpoint is the time to confirmed disease progression defined as either at least a 20% increase in the timed 25-Foot Walk (T25-FW) or at least a 20% increase in the 9-Hole Peg Test (9-HPT; assessment of upper limb function). In each situation the change cannot be attributed to another etiology (for example, fever, concurrent illness, relapse), and is sustained for at least ≥12 weeks up to the end of the trial.

In the T25-FW the patient is directed to one end of a clearly marked 25-foot course and is instructed to walk 25 feet (7.26 m) as quickly as possible, but safely. The time is calculated from the instruction to start and ends when the patient has reached the 25-foot mark. The task is immediately administered again by having the patient walk back the same distance. The score for the T25-FW is the average of the two completed trials. Patients may use assistive devices when doing this task. Because mobility may be affected by factors such as spasticity and the use of different walking aids, subsequent tests between weeks 12 and 120 will be performed with the same walking aid if any, and on the same dose of anti-spasticity medication if any.

In the 9-HPT, the patient is seated at a table with a small, shallow container holding nine pegs and a wood or plastic block containing nine empty holes. On a start command when a stopwatch is started, the patient picks up the nine pegs one at a time as quickly as possible, puts them in the nine holes, and, once they are in the holes, removes them again as quickly as possible one at a time, replacing them into the shallow container. The total time to complete the task is recorded. Two consecutive trials with the dominant hand are immediately followed by two consecutive trials with the non-dominant hand. The overall 9-HPT score is the average of the four trials.

### Secondary outcome parameters

The following secondary clinical endpoints will be assessed: (1) the proportion of patients without sustained 20% increase in the T25-FW, or without 20% increase in the 9-HPT between weeks 12 and 108; (2) the proportion of patients with a stable Hauser ambulation index; (3) cognitive changes measured through a cognitive battery; and (4) fatigue.

The Hauser ambulation index is a rating scale to assess mobility by evaluating the time and degree of assistance required to walk 25 feet. Scores range from 0 (asymptomatic and fully active) to 10 (bedridden). The patient is asked to walk a marked 25-foot course as quickly and safely as possible. The examiner records the time and type of assistance (for example, cane, walker, crutches) needed.

The cognitive battery consists of the Symbol Digit Modalities Test (SDMT), California Verbal Learning Test–II (CVLT-II), and Controlled Oral Word Association Test (COWAT). The Beck depression inventory-II (BDI-II) will be used to get a view on the depression level of the patient.

Fatigue will be assessed with the Modified fatigue Impact Scale (MFIS).

Secondary surrogate endpoints comprise brain magnetic resonance imaging (MRI) data, and in some selected centers changes in the retinal nerve fiber layer thickness and macular volume between weeks 12 and 108 will be measured using optical coherence tomography (OCT).

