### Sample size

The sample size was estimated on the basis of a study in untreated patients with primary progressive multiple sclerosis [23]. The primary event is sustained worsening on the T25-FW or 9-HPT within 2 years using a survival analysis. At 2 years the fraction of event-free patients is estimated to be 45% in the untreated group, and 70% in the fluoxetine-treated group. Using sample size calculation for comparing two survival curves (StatemateTM, GraphPad software, San Diego, CA, USA), including 60 patients in each group has 80% power to detect an increase in survival proportion of 0.25 with a significance level (alpha) of 0.05 (two-tailed). For every patient who drops out within the first 3 months, which is the period when we expect most drop-outs, a new patient will be included until a sample size of 120 patients is reached.

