### Blinding and statistical methods

Patients and the entire study staff will remain blinded throughout the complete treatment period. Treatment allocations will only be disclosed after the final database lock. Independent examiners will do MRI and OCT evaluations. All data will be statistically analyzed by an independent biometrician. Proportion of patients will be analyzed with the use of a chi-square test. A log-rank test will be applied to compare differences in time to confirmed disease progression between the two treatment groups. A Cox proportional hazard model will be used to estimate the reduction in hazard associated with treatment compared with placebo. Repeated measures analysis of covariance will be used to compare differences between the fluoxetine and placebo group in endpoints related to changes from baseline. The test level for statistical significance of differences between both treatment arms is defined as *P* = 0.05 for all tests.

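### Secondary endpoint 1 is misworded: read literally it is not the complement of the primary event, and the 9-HPT half omits the persistence requirement

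*Protocol article*

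**What the plan says.** Under *Secondary outcome parameters*, the first clinical endpoint is "the proportion of patients without sustained 20% increase in the T25-FW, or without 20% increase in the 9-HPT between weeks 12 and 108". *Without* appears on both sides of *or*. *Sustained* appears only before the walk.

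Under *Primary outcome parameter*, progression is "defined as either at least a 20% increase in the timed 25-Foot Walk (T25-FW) or at least a 20% increase in the 9-Hole Peg Test". Two conditions then apply to both tests: "In each situation the change cannot be attributed to another etiology", and the change "is sustained for at least ≥12 weeks up to the end of the trial".

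Under *Sample size*, the same event is used: "The primary event is sustained worsening on the T25-FW or 9-HPT within 2 years using a survival analysis". The planning values are that "the fraction of event-free patients is estimated to be 45% in the untreated group, and 70% in the fluoxetine-treated group".

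Under *Blinding and statistical methods*, the test for this kind of endpoint is given: "Proportion of patients will be analyzed with the use of a chi-square test". No other section restates or corrects secondary endpoint 1.

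**The concern.** A secondary endpoint that counts patients without progression would be expected to mirror the primary event. This one does not, in two respects.

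- **The connective.** If progression is A or B, freedom from progression is not-A and not-B. The article writes not-A or not-B, which equals not-(A and B). A patient whose walk has worsened with confirmation and whose hand function is stable is a primary event, yet meets the secondary endpoint as worded.
- **The persistence rule.** The primary requires it for each test. The secondary states it for the walk only, so the 9-HPT half could be judged on a single unconfirmed rise.

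At stake are the meaning and sensitivity of the first secondary endpoint. There is also the risk that one of several readings is picked after results are known.

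**Working it through.** **Inputs from the article.** Event-free at 2 years 45% (untreated) and 70% (fluoxetine); 60 patients per arm; two-sided alpha 0.05; chi-square test for proportions. The overlap of T25-FW and 9-HPT events is not given and has to be assumed.

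**1. The plan's own figure.** Two-proportion formula with pooled variance under the null and no continuity correction: power = Φ[(d − 1.96·se0)/se1].
- Mean proportion = (0.45 + 0.70)/2 = 0.575
- se0 = √(0.575 × 0.425 × 2/60) = 0.0903
- se1 = √[(0.45 × 0.55 + 0.70 × 0.30)/60] = 0.0873
- Power = Φ[(0.25 − 0.1769)/0.0873] = Φ(0.837) = 79.9%

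The stated 80% reproduces. The log-rank formulas bracket it: with HR = ln 0.70/ln 0.45 = 0.447 and 60 × 0.55 + 60 × 0.30 = 51 events, Schoenfeld gives 82.1% and Freedman 78.0%. A secondary endpoint that was the true complement of the primary would have these proportions and about this chi-square power.

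**2. Direction of the error.** A literal failure needs a sustained walk increase together with a 9-HPT increase. Any sustained walk increase is already a primary event, so literal failures are a subset of primary events, even if the 9-HPT rise need not persist. The literal progression-free proportion therefore cannot fall below 45% or 70%. It equals them only if every patient with a primary event fails on both tests.

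**3. Size, same overlap in each arm (assumed).** Let s be the share of primary events that occur on both tests. The literal proportions are 1 − 0.55s and 1 − 0.30s.

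| s | Placebo | Fluoxetine | Power, 60 per arm |
|---|---|---|---|
| 10% | 94.5% | 97.0% | 10% |
| 20% | 89.0% | 94.0% | 16% |
| 30% | 83.5% | 91.0% | 23% |
| 50% | 72.5% | 85.0% | 39% |
| 100% | 45.0% | 70.0% | 80% |

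In patients: 33 primary events are expected on placebo (60 × 0.55) and 18 on fluoxetine (60 × 0.30). At s = 30%, 33 × 0.7 ≈ 23 and 18 × 0.7 ≈ 13 of them would be counted as progression-free.

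**4. Size, other assumptions.**
- Independent, equally frequent events: event-free on each test √0.45 = 0.671 and √0.70 = 0.837. Literal proportions are 1 − 0.329² = 89.2% and 1 − 0.163² = 97.3%; power 43%.
- Independent, placebo risks 40% (walk) and 25% (pegs), HR 0.447 on each: fluoxetine risks 1 − 0.60^0.447 = 20.4% and 1 − 0.75^0.447 = 12.1%. Literal proportions are 1 − 0.100 = 90.0% and 1 − 0.025 = 97.5%; power about 40%.
- Worsening on both tests in 20% and 7%: 80% and 93%; power 55%.

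**5. Limits of these figures.** All use sustained-event rates, so they do not model an unconfirmed 9-HPT criterion, which would add failures. At 90.0% and 97.5% the mean expected number of failures is 60 × 0.0625 = 3.75 per arm, too few for the normal approximation to be precise. A loss of power is also not a mathematical necessity: if the overlap were much greater on placebo, say s = 60% against 30% on fluoxetine, the proportions would be 1 − 0.33 = 67% and 1 − 0.09 = 91%, and the same formula gives 91% power. Nothing in the article supports or excludes such a pattern.

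**The case against.** The strongest reply is that nobody would program it this way. The sentence may be everyday English for being without either kind of increase, which fits the primary definition and the event-free fractions used for sample size. Or it may mean two proportions, one per test; the comma and the repeated *without* fit that. On either reading a patient who progressed on one test is not wrongly credited with overall freedom from progression. This stands as a limit: the literal reading is what the words say, not proof of what will be analysed. It does not remove the point, because the article does not choose between the readings, and *sustained* is missing for the 9-HPT under all of them.

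A reader might infer more than the text supports:

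- *That the endpoint loses most of its power.* The overlap is unknown, and several scenarios lose half or less (80% to 40%, 43% or 55%).
- *That one unconfirmed 9-HPT rise makes a patient a failure.* Under the literal *or*, it does so only alongside a sustained walk increase.
- *That closing at week 108 conflicts with confirmation at week 120.* The article describes week 120 as an optional visit to confirm progression first seen at week 108. The secondary window can be read as the period in which worsening appears.
- *That the chi-square test is wrong because some patients leave early.* Handling of early leavers is commonly left to the analysis plan or full protocol, which are not shown. The time-to-event comparison already has log-rank and Cox analyses.

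**Conclusion.** The point holds as an error of wording in a secondary endpoint. Read literally, the definition is not the complement of the primary event: a patient with confirmed progression on one test still qualifies. The persistence rule is missing for the 9-HPT on any reading.

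If the literal rule were programmed, the progression-free proportions would exceed 45% and 70% unless the two events overlap completely. That follows from logic alone. The power figures rest on assumed overlap: about 10% to 55% in the main scenarios short of full overlap, against 80% for the true complement. They indicate what could happen and do not predict it.

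The primary endpoint, the primary analysis and the sample size are unaffected. The correction is worth making before unblinding, but it does not threaten the trial's main conclusion and ranks below a must-fix.

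**What to change.** Replace the sentence with: the proportion of patients with neither a sustained (≥12 weeks) ≥20% increase in the T25-FW nor a sustained (≥12 weeks) ≥20% increase in the 9-HPT, using the same reference visit and confirmation rule as the primary endpoint. If one proportion per test is what is meant, list two endpoints and attach the persistence requirement to each. Record the choice before unblinding, so that the reading cannot depend on the results.

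The cost is one sentence in the endpoint list. No new data, visits or change of test are needed.

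### Secondary endpoint 1 is not the complement of the primary event: read literally, a patient who progressed on one test counts as progression-free, and confirmation is required for the walk only

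*Protocol article*

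**What the plan says.** Under Primary outcome parameter, the protocol article defines progression as "either at least a 20% increase in the timed 25-Foot Walk (T25-FW) or at least a 20% increase in the 9-Hole Peg Test". It then sets conditions that apply to both tests: "In each situation the change cannot be attributed to another etiology", and the change "is sustained for at least ≥12 weeks up to the end of the trial".

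The Sample size section uses the same event: "The primary event is sustained worsening on the T25-FW or 9-HPT within 2 years using a survival analysis". It plans on "the fraction of event-free patients is estimated to be 45% in the untreated group, and 70% in the fluoxetine-treated group".

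Under Secondary outcome parameters, the first clinical endpoint is "the proportion of patients without sustained 20% increase in the T25-FW, or without 20% increase in the 9-HPT between weeks 12 and 108". The section on blinding and statistical methods assigns proportions of patients to a chi-square test. No other section restates or explains this endpoint.

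**The concern.** The endpoint appears to be the proportion counterpart of the primary time-to-event endpoint, but its wording differs in two ways.

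- **The connective.** If A is worsening on the walk and B is worsening on the peg test, the primary event is A or B. Its complement is neither A nor B. The secondary endpoint negates each condition and joins them with an *or*, which is literally the complement of A and B together.
- **The confirmation.** The primary endpoint requires a sustained change for both tests. The secondary endpoint attaches that word to the T25-FW only.

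A programmer who follows the sentence literally would count some patients as events in the primary analysis and as progression-free in the first secondary analysis. The percentages could then not be read beside the survival curves. If the reading is settled only at the analysis, the choice could be influenced by the data.

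**Working it through.** **Inputs from the protocol article.** Event-free at 2 years: 45% untreated and 70% on fluoxetine; 60 per group; two-sided alpha 0.05; 80% power (all from Sample size). Event rates are therefore 55% and 30%.

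**Input not in the article.** The share *f* of progressors who worsen on both tests. The Discussion gives only an either-test rate from the cited cohort (56% at 2 years). I take *f* as an assumption, equal in both arms, and show the range.

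**Step 1: reproduce the plan's figure.** For two proportions with mean p̄ = 0.575 and difference 0.25:

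- n = [1.96·√(2·0.575·0.425) + 0.8416·√(0.45·0.55 + 0.70·0.30)]² / 0.25² = (1.370 + 0.569)² / 0.0625 ≈ 60.2, so 61 per arm.
- Power at 60 per arm = Φ[(0.25 − 1.96·0.0903) / 0.0873] = Φ(0.837) = 79.9%, where 0.0903 = √(2·0.575·0.425/60) and 0.0873 = √(0.4575/60).

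The stated 60 per group and 80% power are reproduced closely. A *neither/nor* endpoint, confirmed on both tests, keeps 45% vs 70% and this power.

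**Step 2: classify patients under each reading.**

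| Patient | Primary event? | Literal *or* | Neither/nor, sustained on both |
|---|---|---|---|
| Sustained walk worsening, hands stable | Yes | Counted as progression-free | Not counted |
| Sustained peg-test worsening, walk stable | Yes | Counted as progression-free | Not counted |
| Sustained worsening on both | Yes | Not counted | Not counted |
| No sustained worsening on either | No | Counted | Counted |

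The two columns differ for every patient who progressed on exactly one test.

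**Step 3: size of the *or* alone.** For this step, confirmation is assumed on both tests. The literal proportion is 1 − f × event rate, that is 1 − 0.55f and 1 − 0.30f. Power uses the formula of Step 1 with 60 per arm. Primary events counted as progression-free number 60 × 0.55 × (1 − f) and 60 × 0.30 × (1 − f).

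| Overlap f (assumed) | Placebo vs fluoxetine | Difference (points) | Power | Primary events counted as progression-free, per 60 |
|---|---|---|---|---|
| 10% | 94.5% vs 97.0% | 2.5 | 10% | 29.7 and 16.2 |
| 30% | 83.5% vs 91.0% | 7.5 | 23% | 23.1 and 12.6 |
| 50% | 72.5% vs 85.0% | 12.5 | 39% | 16.5 and 9.0 |
| 75% | 58.8% vs 77.5% | 18.8 | 60% | 8.2 and 4.5 |
| 100% | 45.0% vs 70.0% | 25.0 | 80% | 0 and 0 |

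The overlap need not be equal in the two arms. If the tests were independent with equal rates, the per-test rate would be 1 − √0.45 = 0.329 and 1 − √0.70 = 0.163. The literal proportions would then be 1 − 0.329² = 89.2% and 1 − 0.163² = 97.3%, with power about 43%.

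**Step 4: the missing confirmation.** Under the literal *or*, failure needs a sustained walk increase plus any 9-HPT increase, confirmed or not. That makes failure more common than in Step 3 and so partly offsets the *or*. Under a *neither/nor* reading that still omits confirmation of the 9-HPT, a patient with one passing 9-HPT rise is not counted as progression-free although no primary event occurred. Under two per-test proportions, the walk proportion uses confirmed change and the peg-test proportion does not. In none of these cases does the endpoint match the primary definition.

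**The case against.** The strongest reply is that the literal Boolean reading is only one reading. In ordinary English, negated conditions joined by *or* often mean *neither*. The Primary outcome parameter and Sample size sections make clear what event-free means there, and the authors probably intended the complement of the primary event. Two separate per-test proportions are also possible. Under either of these readings, a one-test progressor is no longer counted as progression-free. This stands, and it is why the *or* problem is stated as a consequence of the literal text. It does not rescue the sentence: the wording does not choose between the readings, and none of them, taken as written, supplies confirmation for the 9-HPT.

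It can also be said that a condensed article leaves operational detail to the full protocol or analysis plan. That would answer a missing detail. Here the article states a definition, and it differs from the one used for the primary event.

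A reader might go further and infer that most progressors would be labelled progression-free. That holds only if fewer than half of them worsen on both tests, and the article gives no such figure. A reader might also add chance 9-HPT rises to the power loss as a second, cumulative harm. That is not supported. Under the literal *or*, a patient with a stable walk and a chance peg-test rise still counts as progression-free, and the two faults pull in opposite directions. Any figure for chance rises would also need a test-retest variability and a visit scheme that the article does not give for this endpoint.

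**Conclusion.** The endpoint is wrong as written, within limits. Its literal wording conflicts with the primary event on the connective, and it omits confirmation for the 9-HPT under every literal reading.

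The *or* alone could leave the planned 25-point difference unchanged (complete overlap) or cut it to 2.5 points (10% overlap), with power between about 80% and 10%. These figures rest on the plan's 45% and 70%, 60 per arm with complete data, an uncorrected two-proportion test, and an assumed overlap equal in both arms. They set aside the missing 9-HPT confirmation, which acts the other way, so they do not predict what a fully literal analysis would give.

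A reader might infer that the trial's main result is at risk. The article does not support that: the primary endpoint, its log-rank test and the sample size are stated consistently on this point, and the sample size reproduces. Only this secondary endpoint is affected.

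**What to change.** Reword the endpoint to:

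> The proportion of patients with neither a sustained increase of at least 20% in the T25-FW nor a sustained increase of at least 20% in the 9-HPT between weeks 12 and 108, with attribution and confirmation as in the primary endpoint.

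If two component proportions are intended, list them as two endpoints and require a sustained change in both.

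The cost is one sentence in the protocol and the matching line in the analysis plan. No new data are needed, because both tests are already required for the primary endpoint. The Trial status section says recruitment is still under way, so the wording can be settled before treatment allocations are disclosed.
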